## Abstract

**Background:**

After hospitalization for cardiac disease, older patients are at high risk of readmission and death. Although geriatric conditions increase this risk, treatment of older cardiac patients is limited to the management of cardiac diseases. The aim of this study is to investigate if unplanned hospital readmission and mortality can be reduced by the Cardiac Care Bridge transitional care program (CCB program) that integrates case management, disease management and home-based cardiac rehabilitation.

**Methods:**

In a randomized trial on patient level, 500 eligible patients ≥ 70 years and at high risk of readmission and mortality will be enrolled in six hospitals in the Netherlands. Included patients will receive a Comprehensive Geriatric Assessment (CGA) at admission. Randomization with stratified blocks will be used with pre-stratification by study site and cognitive status based on the Mini-Mental State Examination (15–23 vs ≥ 24). Patients enrolled in the intervention group will receive a CGA-based integrated care plan, a face-to-face handover with the community care registered nurse (CCRN) before discharge and four home visits post-discharge. The CCRNs collaborate with physical therapists, who will perform home-based cardiac rehabilitation and with a pharmacist who advices the CCRNs in medication management The control group will receive care as usual.

The primary outcome is the incidence of first all-cause unplanned readmission or mortality within 6 months post-randomization. Secondary outcomes at three, six and 12 months after randomization are physical functioning, functional capacity, depression, anxiety, medication adherence, health-related quality of life, healthcare utilization and care giver burden.

**Discussion:**

This study will provide new knowledge on the effectiveness of the integration of geriatric and cardiac care.

**Trial registration:**

NTR6316. Date of registration: April 6, 2017.

**Electronic supplementary material:**

The online version of this article (10.1186/s12913-018-3301-9) contains supplementary material, which is available to authorized users.

## Background

Cardiac disease is the leading cause of hospitalization and mortality [1]. In the population of older hospitalized cardiac patients, 20% are readmitted and 10% die within 1 month post-discharge [2]. In addition to cardiac disease, geriatric conditions such as impaired activities of daily living (ADL) (77%), cognitive impairment (42%) and fall risk (30%) are highly prevalent [3]. The assessment of geriatric conditions is not currently part of routine medical evaluation in cardiology. As a result, these conditions are often unrecognized [4, 5] leading to an increased risk of new disabilities, readmission and death [3, 6].

The transition of care in which patients transfer between different settings increases the risk for adverse health outcomes due to inadequate attention to patients’ healthcare needs [7, 8]. For example, the failure to recognize geriatric conditions in older cardiac patients negatively impacts treatments post-discharge, e.g. because of nonadherence to (pharmacological) treatment in cognitively impaired patients [4] or poor participation in cardiac rehabilitation programs because of disabilities, the high intensity of these programs [9, 10], fatigue [11] and difficulties traveling to and from cardiac rehabilitation centers [12, 13]. This is unfortunate since cardiac rehabilitation has been shown to reduce cardiovascular risk factors, readmission and mortality in older cardiac patients [14].

Adequate guidance during hospitalization, during the transition from hospital to home and in the early post-discharge period may potentially reduce the risk of adverse events. Transitional care is a model that aims to continue care when patients transfer between different care settings, with a focus on patients’ needs [15, 16]. Recently, the Transitional Care Bridge program resulted in a 25% (HR 0.75, 95% CI 0.56–0.99, *P* = 0.045) reduction in mortality in acutely hospitalized older patients, by combining a Comprehensive Geriatric Assessment (CGA), an integrated care plan and a transitional care program, including visits during hospitalization and soon after discharge by a community care registered nurse (CCRN) [17]. However, with this case management approach no effects were found on readmission rates and ADL-functioning. We hypothesize that this may be caused by a main focus on case management within the care transition program with a lack of attention for disease management and rehabilitation after discharge.

The RESPONSE study of Jorstad et al. [18] involved a nurse-coordinated outpatient intervention that included guidance on lifestyle factors, biometric risk factors and therapy adherence in patients after an acute coronary syndrome. In this disease management approach, a relative risk reduction of 17.4% (*P* = 0.021) was found on the Systematic Coronary Risk Evaluation (SCORE), which is an integrated measure to estimate the risk of cardiovascular death in 10 years. In addition, a relative risk reduction of 34.8% (*P* = 0.023) was found on readmission.

Combining case management, disease management and home-based rehabilitation may have the potential to reduce readmission and mortality. Therefore, we developed the nurse-coordinated Cardiac Care Bridge transitional care program (CCB program) aiming to reduce unplanned hospital readmission and mortality in the first six months in comparison to usual care in older hospitalized cardiac patients at high risk of readmission and mortality. In this paper we report on the design of this program.

## Methods/Design

This study follows the Standard Protocol Items for Interventional Trials (SPIRIT) checklist (Additional file 1) [19]. The next paragraphs describe the Cardiac Care Bridge program, the study design and research methods.

### Design and setting

A single-blinded multi-center parallel group superiority trial with randomization at patient level will be performed in six hospitals in the Amsterdam region of the Netherlands: 1) Academic Medical Center (AMC), Amsterdam, 2) Amstelland Medical Center, Amstelveen, 3) BovenIJ Medical Center, Amsterdam, 4) Medical Center Slotervaart, Amsterdam, 5) Onze Lieve Vrouwe Gasthuis (OLVG), Amsterdam, 6) Tergooi Medical Center, Blaricum. In the transitional and post-clinical phase, five community nursing care organizations will participate: 1) Amstelring, 2) Buurtzorg Nederland, 3) Cordaan Home Care, 4) Evean, 5) Vivium Care Group. In the post-clinical phase, several community based physical therapists (PT) will participate. The recruitment for the study started on June 5, 2017 and will end after the last patient has been followed-up for 12 months, which is expected in December, 2019.

### Study population

Potential participants are all cardiac patients 70 years and older, acutely or electively admitted to the departments of cardiology or cardiothoracic surgery and admitted ≥ 48 h. They are eligible for inclusion if they are at high risk of functional decline according to screening instrument for frail elderly of the Dutch Safety Management Program (VMS instrument, Table 1). Four geriatric conditions (ADL, falls, malnutrition and delirium) are part of this screening. Oud et al. [20] also found a positive association between an increase of the number of risk factors with the VMS instrument and risk of death. Heim et al. [21] studied the optimal predictive value of frailty on adverse outcomes (death, functional decline and high healthcare use) with the VMS instrument. The strongest predictive value was found by a positive score on ≥ 3 risk factors in patients aged 70–79 and a positive score on ≥ 1 risk factor in patients aged ≥ 80 years. However, the screening of malnutrition may not be sensitive in cardiac patients because of an increased risk of weight gain due to decompensated heart failure [22]. Therefore, we considered patients aged 70–79 years with ≥ 2 risk factors and patients aged ≥ 80 years with ≥ 1 risk factor eligible for inclusion. In addition, patients at high risk of readmission and mortality are eligible to participate if they have had an unplanned hospital admission in the previous 6 months. This risk factor is associated with an increased risk of further readmissions and mortality [23, 24].

**Table 1 Tab1:** Screening tool for vulnerable elderly of the Dutch Safety Management Program

Risk domain	Instrument	Questions	Cut-off	Score^a^
Fall risk	Single question	Did you fall in the last 6 months?	yes = 1	1
Malnutrition	SNAQ [53]	Assessing whether the patient: 1) lost weight unintentionally in the last 36 months and/or 2) experiences a decreased appetite and 3) used supplemental drinks or tube feeding	Question 1 = yes or Question 2 + 3 = yes	1
Delirium	Single questions	Assessing whether: 1) the patient has cognitive impairment; 2) the patient needed help with self-care in the last 24 h; 3) the patient has previously undergone a delirium	≥ 1 point = 1	1
ADL-functioning	KATZ-6 [54]	Assessing whether the patient needs help with: 1) bathing, 2) dressing, 3) toileting, 4) transferring from bed to a chair, 5) eating, and 6) whether the patient uses incontinence material	≥ 2 points = 1	1
Total score				0–4

*Abbreviations SNAQ* Short nutritional assessment questionnaire, *ADL* Functioning activities of daily living-functioning, *KATZ-6* Modified KATZ-6 index

^a^Patients are at high risk of functional decline if aged 70–79 years and score ≥ 2 or aged ≥ 80 years and score ≥ 1

Exclusion criteria are the following: 1) severe cognitive impairment, assessed with the Mini-Mental State Examination (MMSE < 15), 2) congenital heart disease, 3) terminal illness, defined as a life expectancy of less than 3 months as estimated by the treating physician, 4) transfer from or a planned discharge to a nursing home, 5) planned discharge to another department or another hospital not participating in this study, 6) inability to communicate in Dutch, 7) delirium as confirmed by patient’s physician and not resolved within 4 days after hospital admission.

### Randomization and blinding

After patients are screened for eligibility and have provided informed consent to a cardiac research nurse (CRN), the baseline assessment will be performed. After the baseline assessment patients will be randomized to the intervention or control group. Stratified block randomization (1:1) will be used with pre-stratification by study site and cognitive status based on the MMSE (15–23 vs ≥ 24). To ensure allocation concealment, a web-based data management program (Research Manager, http://deresearchmanager.nl/nl/home/) [25] and random permuted blocks of variable sizes will be used.

Group assignment will be blinded to patients. They will be informed that the study aim is to study different forms of post-discharge care and will receive only general information about the study protocol according to the postponed informed consent procedure of Boter et al. [26] Patients will be blinded to the aim of the intervention to prevent a potential Hawthorne effect [27, 28]. At the end of follow-up, patients (or their caregivers) will be fully informed about the content of the study intervention and the allocated treatment they received. Healthcare practitioners who execute the intervention cannot be blinded. Outcome assessments will be performed by research nurses who are blinded to the allocated treatment. Statistical analyses will be performed according to a predefined statistical analysis plan (see Statistical Analysis paragraph) by investigators blinded to group assignment.

Due to the minimal expected side effects related to the intervention of the CCB care program a data monitoring committee is not mandatory for this trial.

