### Sample size calculation

The sample size calculation is based on findings in a relevant subpopulation (101/674) of cardiac patients of the Transitional Care Bridge program [17], a comparable study including hospitalized patients ≥ 65 years at high risk of functional decline. Based on a six-month incidence rate of 44% (readmission and mortality combined) in the usual care subpopulation of the Transitional Care Bridge program and a minimal important difference of 12.5% in absolute risk reduction (from 44 to 31.5%) in patients in the intervention arm, (2-sided alpha of 0.05; power of 80%), a sample size of 235 patients per group is required. To compensate for an assumed 5% loss to follow-up, the total sample size per group will be 250 (Fig. 1).

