### Statistical analyses

All analyses will be performed according to a predefined statistical analysis plan, which is published in the Netherlands Trial Register (NTR6316). The primary analyses will be performed according to the intention-to-treat principle. Outcomes will be reported as unadjusted risk differences and their 95% confidence intervals. Adjusted analyses using multivariable logistic or linear regression models, as appropriate, will focus on the incidence proportion of the composite endpoint of readmission and mortality up to 6 months. All analyses will be adjusted for the following potential confounders: age, sex, Charlson Comorbidity Score, MMSE, cardiovascular diagnosis, length of stay and living arrangement. In addition, subgroup analyses will be performed for cardiac diagnosis, frailty status with the VMS screening tool, cognitive status with the MMSE and social economic status. Data will be collected by an electronic Case Record Form in Research Manager [25], a web-based data management program. Multiple imputation will be used as a sensitivity analysis to assess the impact of missing values.

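### Randomization is stratified by study site, but the unadjusted risk difference and the fixed covariate list both leave site out; the analysis stays valid, and the loss is at most small

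*Protocol article*

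**What the plan says.** Under Randomization and blinding, the protocol article states: "Stratified block randomization (1:1) will be used with pre-stratification by study site and cognitive status". The cognitive split is MMSE 15–23 versus 24 or more. Design and setting names six hospitals, so there are 6 × 2 = 12 randomization strata.

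Under Statistical analyses, outcomes are to be given as unadjusted risk differences with 95% confidence intervals. Adjusted logistic or linear models follow, and the adjustment variables are named in full: "age, sex, Charlson Comorbidity Score, MMSE, cardiovascular diagnosis, length of stay and living arrangement". MMSE, one of the two stratification factors, is on the list. Study site, the other, is not, and no reason is given.

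Under Study population, an unplanned admission in the previous 6 months is described as a route to eligibility, with the remark: "This risk factor is associated with an increased risk of further readmissions and mortality". This variable is neither a stratification factor nor on the covariate list.

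**The concern.** Stratified randomization balances the arms within each site. If sites differ in event risk, that balance reduces the true sampling variation of the treatment difference. An analysis that ignores site does not credit the reduction, so its standard error is somewhat larger than it need be and its interval somewhat wide. The usual remedy is to analyse by the factors used to randomize. Here one factor was carried into the adjusted model and the other was not.

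The article gives some reason to think that site could matter. The hospitals include an academic center and several medical centers, they cover urban and rural areas (Strengths and limitations), inclusion started stepwise by hospital (Training for healthcare providers and implementation), and a cardiac nurse specialist is part of usual care only where available (Usual care). None of this is quantified.

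At stake are a little precision on the primary risk difference, agreement between design and analysis, and removal of a choice about site that would otherwise be made after the data are seen.

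**Working it through.** **Inputs from Sample size calculation.** Two-sided alpha 0.05 and power 80%. The control rate is given as "Based on a six-month incidence rate of 44% (readmission and mortality combined) in the usual care subpopulation". The target reduction is 12.5 percentage points, to 31.5%. The result is "a sample size of 235 patients per group is required", and then "To compensate for an assumed 5% loss to follow-up, the total sample size per group will be 250".

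**Step 1: reproduce the plan's figure.** Mean risk p̄ = (0.44 + 0.315)/2 = 0.3775, and p̄(1 − p̄) = 0.2350. With the pooled-variance formula and no continuity correction:

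n = [1.960·√(2 × 0.2350) + 0.8416·√(0.44 × 0.56 + 0.315 × 0.685)]² / 0.125² = 1.9158² / 0.015625 = 234.9, so 235 per group.

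Power at 235 is 80.0%. Allowing for 5% loss, 235/0.95 = 247.4, or 248, which the plan rounds to 250. The figure reproduces, and it does so for an unadjusted comparison. It borrows nothing from stratification.

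**Step 2: what accounting for site could add.** The documents give no between-site variation, so a range is assumed. With a between-site standard deviation of risk s, the share of outcome variance explained is R² = s²/0.2350, and the effective size is 235/(1 − R²) per group.

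| Assumed s (points) | R² | Effective n per group | Power |
|---|---|---|---|
| 0 | 0% | 235.0 | 80.0% |
| 3 | 0.4% | 235.9 | 80.2% |
| 5 | 1.1% | 237.5 | 80.4% |
| 8 | 2.7% | 241.6 | 81.1% |
| 10 | 4.3% | 245.4 | 81.7% |

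**Step 3: simulation check.** The set-up was 470 patients, six sites, permuted blocks within site and MMSE stratum, 3,000 runs per scenario, and a linear risk-difference model with robust standard errors. Prior admission was given 40% prevalence and raised risk by 10 points in the moderate scenario and 15 points in the strong one.

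| Scenario | Rejection, unadjusted | Rejection, with site | Mean SE, unadjusted | Mean SE, with site |
|---|---|---|---|---|
| Moderate (s = 5 points) | 79.9% | 80.3% | 0.04423 | 0.04410 (0.3% lower) |
| Strong (s = 10 points) | 80.5% | 81.6% | 0.04423 | 0.04334 (2.0% lower) |

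The strong-scenario gain of 1.1 points is a little below the 1.7 in Step 2. Balance on site already steadies the unadjusted estimate: its power becomes Φ(0.842/√(1 − 0.0426)) = Φ(0.861) = 80.5%. So 1.7 is an upper figure within the assumed range.

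**Step 4: type I error.** Under no effect, the unadjusted test rejected in 4.6% to 5.0% of runs, with a Monte Carlo standard error of √(0.05 × 0.95/3000) = 0.4 points. In theory, at s = 10 points the rate is 2[1 − Φ(1.960/√0.9574)] = 4.5%. Any departure is small and on the conservative side.

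**Step 5: cost in parameters.** Six sites use 5 degrees of freedom. Expected events among 470 evaluable patients are 235 × (0.44 + 0.315) = 177.

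**The case against.** The strongest reply is that a predefined statistical analysis plan exists in the trial register and is not shown. The seven variables are labelled potential confounders, and handling of stratification factors is often left to that plan. This has weight: the registered plan may already include site. However, the article gives a complete list rather than examples, and its section on blinding sends the reader to that same paragraph for the plan. If the registered plan does include site, the published text should be brought into line with it.

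A second reply is that the gain is small and conditional. That stands. It is zero if sites do not differ in risk. Step 2 also measures it against a model with no covariates, so on top of the seven listed variables it could be smaller still. The effective-size formula suits a linear or standardized risk difference. In the planned logistic model, adding site may raise power but does not narrow the interval for the log odds ratio.

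Stronger readings are tempting but not supported:

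- *The planned test is invalid.* It is not; its type I error is at or slightly below nominal.
- *The trial is underpowered because site is ignored.* The 235 per group already assumes no adjustment.
- *Several points of power are lost.* An R² of 10% would give 84.0%, but from site alone that needs a between-site standard deviation of √(0.10 × 0.2350), or 15.3 points. Nothing in the article suggests this.
- *Leaving out prior unplanned admission wastes precision secured by the design.* Randomization was not stratified on it, so its omission is a choice among prognostic covariates. Nor can it be assumed to be on file for everyone: Table 3 has no baseline row for it, and its readmission item is marked only at the three follow-up contacts.

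**Conclusion.** The mismatch between design and analysis is real: site is used to randomize and then appears in neither the unadjusted risk difference nor the fixed covariate list. Its consequence is minor. The planned analysis is valid, and it is slightly conservative only if event risk varies between hospitals. The upper end of the power range, 81.7%, needs an assumed between-site standard deviation of 10 points; the documents supply no value for it. The sample size of 235 per group, or 250 after loss to follow-up, stands. The case for changing the text rests on consistency and negligible cost more than on the size of the gain.

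**What to change.** - Add study site (six levels) to every adjusted model, alongside MMSE. Set in advance a rule for pooling very small sites.
- Report the primary risk difference stratified by site and MMSE stratum (for example with Mantel–Haenszel weights), or standardized over both from the regression model. The precision gain then falls on the scale that the article reports.
- Optionally, prespecify unplanned admission in the previous 6 months as a prognostic covariate. Do so only if the sponsor confirms that it was recorded at baseline for every patient, including those who qualified on the VMS score.
- If the registered analysis plan already handles site, say so and align the article's list with it.

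The site change is a matter of wording, since site is known for every patient from randomization. It uses about five degrees of freedom against roughly 177 expected events. It should be dated before unblinding. Prior admission would use one more degree of freedom and, if it was not captured for all, would need record review.

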### Hospital care for all included patients

Table 2 shows the time frame and components of the CCB program in the intervention and control groups. All included patients will receive a CGA within 72 h after admission by a CRN, which will also serve as the baseline study measurement (Table 3). The CGA identifies health issues in the somatic, psychological, social and functional domains, including problems related to polypharmacy, malnutrition, fall risk, delirium, depression and quality of life. Cardiovascular risk factors (e.g. body mass index, smoking, alcohol use and physical performance) will also be assessed. Following assessment, consenting patients will be randomized to the intervention or control group.

**Table 2 Tab2:** Time frame and components of the Cardiac Care Bridge program and the control group

Time Frame	Intervention component	Baseline – outcome measures	Professionals involved	Intervention	Control
Clinical phase					
≤ 72 h after hospital admission	*CGA* ^a^	Baseline	CRN^b^	X	X
≤ 72 h after hospital admission	Integrated care plan		CRN^b^	X	
During hospital stay	Geriatric team consultation in case of ≥ 5 identified health issues or ≥ 1 psychological issue		CRN^b^, CNS^c^, geriatrician	X	
Discharge phase					
Before hospital discharge	In-person handover of the CGA^a^, integrated care plan and medical treatment plan		CRN^b^, CCRN^d^	X	
Before hospital discharge	Visit of CCRN^d^ to participant		CCRN^d^	X	
At discharge	Medical discharge letter		Cardiologist, GP^e^, CCRN^d^	X	X
Post-clinical phase					
≤ 2 days after hospital discharge	Home visit 1. Medication reconciliation and integrated care plan		CCRN^d^	X	
≤ 1 week	*Home visit 2. Intake home based cardiac rehabilitation and integrated care plan*		CCRN^d^, PT^f^	X	
Week 1	*Two home-based cardiac rehabilitation sessions*		PT^f^	X	
Week 2	*Two home-based cardiac rehabilitation sessions*		PT^f^	X	
Week 3	Home visit 3. lifestyle promotion and self-management		CCRN^d^ PT^f^	X X	
	*Two home-based cardiac rehabilitation sessions*		PT^f^	X	
Week 4	*Two home-based cardiac rehabilitation sessions*		PT^f^	X	
Week 5	*Two home-based cardiac rehabilitation sessions*				
Week 6	Home visit 4. Evaluation of integrated care plan and home-based cardiac rehabilitation		CCRN^d^ PT^f^	X X	
	*Two home-based cardiac rehabilitation sessions*				
≤ 12 weeks	Home visit 5. If indicated by the CCRN^b^				
3 months		Follow-up telephone	Research Nurse	X	X
6 months		Follow-up home visit	Research Nurse	X	X
12 months		Follow-up telephone	Research Nurse	X	X

^a^Comprehensive Geriatric Assessment (CGA)

^b^Cardiac Research Nurse (CRN)

^c^Clinical Nurse Specialist in geriatrics (CNS)

^d^Community Care Registered Nurse (CCRN)

^e^General Practitioner (GP)

^f^Physical therapist (PT)

**Table 3 Tab3:** Baseline assessment, outcome measures and time points in the Cardiac Care Bridge

	CGA	Question or instrument	T0*	T0 + ^†^	T1^‡^	T2^§^	T3^||^
Sociodemographic data							
Age		Date of birth	X^¶^				
Gender			X^¶^				
Postal code			X				
Living arrangement			X				
Marital status			X				
Ethnicity		Patients’ country of birth	X				
Education			X				
Mortality		Date of death	X^¶^		X^¶^	X^¶^	X^¶^
Medical data							
Diagnosis (and history) of cardiac disease			X^¶^				
Comorbidities		CCI [55]	X^¶^				
Date of hospitalization			X^¶^				
Hospitalization department			X				
Functional domain							
ADL- and iADL-functioning	+	ALDS [35]	X		X	X	X
Functional status		Specific Activity Scale [33]	X			X	
Hearing impairment	+	Do you experience difficulties with hearing, despite the use of a hearing aid?	X				
Visual impairment	+	Do you experience difficulties with your vision, despite the use of glasses?	X				
Fatigue	+	NRS	X			X	
Falls	+	Frequency	X		X	X	X
Fear of falling	+	NRS	X		X	X	X
Physical domain							
Nutritional status	+	SNAQ [53]	X		X	X	X
Pain	+	NRS [56]	X			X	
Dizziness	+	Do you currently suffer from dizziness If yes, does this affect your daily living?	X			X	
Shortness of breath	+	Do you currently suffer from shortness of breath? If yes, does this affect your daily living?	X			X	
Angina pectoris	+	Do you currently suffer from angina pectoris If yes, does this affect your daily living?	X			X	
Heart palpitations	+	Do you currently suffer from heart palpitations? If yes, does this affect your daily living?	X			X	
Incontinence	+	Do you suffer from incontinence? If yes, do you suffer from incontinence of urine and/or defecation?	X			X	
Presence of urinary catheter	+	Do you have a urinary catheter? If yes, did you have the urinary catheter before hospitalization?	X			X	
Nycturia	+	Do you currently suffer from nycturia? If yes, does this affect your daily living?	X			X	
Handgrip strength	+	Jamar [57]	X			X	
Psychological domain							
Cognitive status	+	MMSE [58]	X			X	
Depression & apathy	+	GDS-15[41]	X			X	
Anxiety	+	HADS-A [38]	X		X	X	X
Quality of life	+	EQ-5D-5 L [40]	X		X	X	X
Smoking status		Do you smoke or did you smoke in the past? If yes, how many cigarettes per day and for how many years?	X		X	X	X
Alcohol use		AUDIT-C [59]	X		X	X	X
Social domain							
Caregiver burden		TOPIC-MDS [41]	X			X	X
Medication use							
Polypharmacy	+	Do you use five or more different medications?	X			X	
Medication adherence	+	Medication Adherence Questionnaire	X		X	X	X
Side effect of medication	+	Do you experience difficulties or side effects with medication use?	X			X	
Type of medication		Type, frequency and dose of medication	X^¶^		X^¶^	X^¶^	X^¶^
Physical performance							
Physical performance		30-s chair stand test [60]		X		X	
Mobility		SPPB [36]	X			X	
Physical capacity		2 MST [37]	X	X		X	
Perceived exertion		Borg RPE scale [61]	X	X		X	
Dyspnoea		MRC dyspnoea scale [62]		X		X	
Parameters							
BMI		Weight and length	X			X	
Waist circumference			X			X	
Blood pressure		mmHg	X			X	
Heart frequency		BPM	X			X	
Respiratory rate			X			X	
Blood parameters		Hemoglobin	X^¶^		X^¶^	X^¶^	X^¶^
		Albumin	X^¶^		X^¶^	X^¶^	X^¶^
		Creatinine	X^¶^		X^¶^	X^¶^	X^¶^
		Total cholesterol	X^¶^		X^¶^	X^¶^	X^¶^
		LDL-cholesterol	X^¶^		X^¶^	X^¶^	X^¶^
		HDL-cholesterol	X^¶^		X^¶^	X^¶^	X^¶^
		Triglyceride	X^¶^		X^¶^	X^¶^	X^¶^
		Glucose / HbA1C	X^¶^		X^¶^	X^¶^	X^¶^
Healthcare utilization		TOPIC-MDS [41]					
Readmission		Have you been hospitalized in the last six months? If yes, what was the hospitalization diagnosis and in what hospital were you readmitted?			X^¶^	X^¶^	X^¶^
Emergency visits		Have you visited the emergency or cardiac emergency room in the last six months? If yes, how many times and for what reason?			X*	X*	X*
Nursing home admission		Have you been admitted to a nursing home in the last months? If yes, for how many weeks?			X	X	X
General practice consult		Have you had a consult with your general practitioner in the last month? If yes, was this during office hours or during the evening, night or weekend and how many times in total?			X	X	X
Home visit of GP		Have you had a home visit from your GP in last month? If yes, was this during office hours or during the evening, night or weekend, and how many times in total?			X	X	X
Home care		Do you receive home care? If yes, is this care assistance and/or domestic help, and how many hours per week?			X	X	X
Day care		Do you have day care? If yes, how many days per week?			X	X	X
Cardiac rehabilitation use		Do you participate in cardiac rehabilitation in a rehabilitation center or outpatient clinic?			X	X	X
Physical therapy		Do you participate in cardiac rehabilitation in a rehabilitation center or outpatient clinic?			X	X	X

*Abbreviations CCI* Charlson comorbidity index, *ALDS* Amsterdam linear disability scale*, NRS* numeric rating scale, *SNAQ* short nutritional assessment questionnaire, *MMSE* mini mental state examination, *GDS-15* geriatric depression Scale-15, *HADS-A* hospital anxiety and depression scale-anxiety subscale*,* EuroQol-5D Euroqol quality of life, *MDS* minimal dataset, *SPPB* short physical performance battery, *2MST* 2 Minute step test, *Borg RPE scale* ratings of perceived exertion scale, *MRC Dyspnea Scale* Medical Research Council dyspnea scale, *mmHg* millimetre of mercury, *BPM* beats per minute

*T0: baseline, ≤ 48 h after admission; ^†^T0+: within 2 weeks after hospitalization during home-based cardiac rehabilitation intake; ^‡^T1: 3 months after hospitalization, follow-up by telephone; ^§^T2: 6 months after hospitalization, follow-up by home visit; ^||^T3: 12 months after hospitalization, follow-up by telephone. ^¶^Data will be obtained from the medical record

